## Abstract

**Background:**

Organ dysfunction consequent to infection (‘severe sepsis’) is the leading cause of admission to an intensive care unit (ICU). In both animal models and early clinical studies the calcium channel sensitizer levosimendan has been demonstrated to have potentially beneficial effects on organ function. The aims of the Levosimendan for the Prevention of Acute oRgan Dysfunction in Sepsis (LeoPARDS) trial are to identify whether a 24-hour infusion of levosimendan will improve organ dysfunction in adults who have septic shock and to establish the safety profile of levosimendan in this group of patients.

**Methods/Design:**

This is a multicenter, randomized, double-blind, parallel group, placebo-controlled trial. Adults fulfilling the criteria for systemic inflammatory response syndrome due to infection, and requiring vasopressor therapy, will be eligible for inclusion in the trial. Within 24 hours of meeting these inclusion criteria, patients will be randomized in a 1:1 ratio stratified by the ICU to receive either levosimendan (0.05 to 0.2 μg.kg^-1^.min^-1^ or placebo for 24 hours in addition to standard care. The primary outcome measure is the mean Sequential Organ Failure Assessment (SOFA) score while in the ICU. Secondary outcomes include: central venous oxygen saturations and cardiac output; incidence and severity of renal failure using the Acute Kidney Injury Network criteria; duration of renal replacement therapy; serum bilirubin; time to liberation from mechanical ventilation; 28-day, hospital, 3 and 6 month survival; ICU and hospital length-of-stay; and days free from catecholamine therapy. Blood and urine samples will be collected on the day of inclusion, at 24 hours, and on days 4 and 6 post-inclusion for investigation of the mechanisms by which levosimendan might improve organ function. Eighty patients will have additional blood samples taken to measure levels of levosimendan and its active metabolites OR-1896 and OR-1855. A total of 516 patients will be recruited from approximately 25 ICUs in the United Kingdom.

**Discussion:**

This trial will test the efficacy of levosimendan to reduce acute organ dysfunction in adult patients who have septic shock and evaluate its biological mechanisms of action.

**Trial registration:**

Current controlled trials ISRCTN12776039 (19 September 2013)

## Background

Severe sepsis is defined as organ dysfunction consequent to the systemic inflammatory response syndrome triggered by infection. It is responsible for approximately 30% of all admissions to an intensive care unit (ICU) in the United Kingdom (UK) yet, despite improvements in care, the mortality from severe sepsis remains high. According to data from the UK Intensive Care National Audit and Research Centre, the incidence of severe sepsis has increased by 68% over a nine-year period, such that the total number of severe sepsis cases in the UK is in excess of 45,000 per annum with a hospital mortality rate of approximately 45% [1]. Mortality rates increase with an increasing number of organ failures [2,3] whilst the development of acute kidney injury (AKI) doubles the risk of death [4].

### Levosimendan

Levosimendan (Simdax™; Orion Corporation, Espoo, Finland) is a licensed treatment for decompensated heart failure in 48 countries. It sensitizes the myocardium to calcium so that a greater ventricular contraction (and thus stroke volume) can be achieved for the same intracellular calcium concentration. In contrast to catecholamines, levosimendan enhances cardiac performance without significantly increasing myocardial oxygen demand [5]. The drug itself has a short plasma half-life of approximately 1 hour, is approximately 95% bound to plasma proteins and is fully metabolized in the liver and intestine into both active and inactive metabolites. However, the hemodynamic effects are maintained for up to 7 days after a single 24-hour infusion of levosimendan due to the effects of the active metabolite, OR-1896, which has an elimination half-life of approximately 80 hours [6]. Levosimendan also causes vasodilatation, mediated by activation of ATP-sensitive vascular K^+^-channels [7], possesses anti-inflammatory properties [8,9], and has been extensively investigated in patients with acute heart failure due to a variety of etiologies [10].

Myocardial dysfunction is seen in over 50% of patients with severe sepsis [11] and its presence is linked to worse outcomes [12]. Implicated mechanisms include altered calcium trafficking and reduced troponin sensitivity to calcium [13]. The calcium and anti-inflammatory actions of levosimendan provide a strong biological rationale for its use in sepsis. In addition, conventional vasoactive support using catecholamines such as norepinephrine and dobutamine may result in sympathetic nervous system overstimulation and a range of adverse effects [14]. Evidence of a lack of benefit from trials comparing different catecholamine regimens [15], increased mortality in patients exposed to a greater vasopressor load [16], the observation of higher plasma catecholamine levels in non-survivors compared to survivors of critical illness [17], and emerging evidence that beta-blockade may play a role if patients are receiving high-dose catecholamines [18] all provide further evidence of possible harm from conventional catecholamine therapy.

Beneficial effects from the use of levosimendan in severe sepsis have been reported in animal models [19-23]. In humans, several case reports, case series [24-27] and small single-centre clinical trials [28-33] provide good evidence to support the hypothesis that levosimendan may be a promising therapy in severe sepsis. Morelli *et al.* conducted a randomized controlled trial comparing an infusion of levosimendan at 0.2 ug.kg^−1^.min^−1^ to dobutamine at 5 μg.kg^−1^.min^−1^ for 24 hours in 28 patients with septic shock and echocardiographically proven acute left ventricular dysfunction [28]. As well as improving hemodynamics, levosimendan increased creatinine clearance by 64% compared to dobutamine at 5 μg.kg^−1^.min^−1^. In a randomized placebo-controlled trial in 35 patients with septic shock and the acute respiratory distress syndrome, levosimendan at 0.2 μg.kg^−1^.min^−1^ increased cardiac index and reduced mean pulmonary artery pressure compared to placebo [29]. In a further randomized controlled study in 40 patients with septic shock, levosimendan at 0.2 μg.kg^−1^.min^−1^ significantly improved microcirculatory flow when compared to dobutamine at 5 μg.kg^−1^.min^−1^[30]. Two similar studies in septic shock (both randomized controlled trials) demonstrated improved hemodynamics with reduced requirements for additional catecholamines [31] and improvements in cardiac output and mixed venous oxygen saturation [32] with the use of levosimendan. Another trial of 30 patients showed improved hepatic function, measured by indocyanine green clearance, with levosimendan compared to dobutamine at 5 μg.kg^−1^.min^−1^[33]. Further evidence to support an improvement in organ function comes from a retrospective analysis of 99 patients with septic shock who received levosimendan at 0.2 μg.kg^−1^.min^−1^ for 24 hours within 36 hours of admission to the ICU [34]. When compared to matched controls, levosimendan-treated patients demonstrated a 24% increase in glomerular filtration rate at 96 hours together with a reduced peak serum creatinine.

### Risks

Levosimendan has been widely used in patients with acute heart failure with a good safety profile and no known significant pharmacokinetic drug interactions. According to the levosimendan investigators’ brochure, between September 2000 (when the drug first received a license in Sweden) and November 2010 an estimated 440,000 patients have received the drug with a reported serious adverse drug reaction rate of 791 out of 440,000 (0.2%). The most common adverse events reported were hypotension (0.03%) and serious arrhythmias (0.02%). Levosimendan has also been used in over 200 patients with septic shock in published controlled trials and case series without any reported significant adverse effects. Adequate cardiovascular resuscitation with intravenous fluids and norepinephrine, as well as avoiding both the initial bolus loading dose and a high-dose infusion (≥0.4 μg.kg^−1^.min^−1^) help reduce adverse effects when used in sepsis [35]. Levosimendan is currently used in many ICUs within Europe in the treatment of severe sepsis and septic shock and has recently been recommended as an alternative inotrope in the German Sepsis Society guidelines [36].

There is therefore good evidence that levosimendan improves cardiac output, regional perfusion, and other physiological endpoints, including renal function, in patients with septic shock. This trial is therefore designed to identify important clinical outcome benefits and to further explore the mechanisms of action of levosimendan in septic shock.

## Methods/Design

The Levosimendan for the Prevention of Acute oRgan Dysfunction in Sepsis (LeoPARDS) trial is a multicenter prospective, randomized, double-blind, parallel group, placebo-controlled trial. The trial is sponsored by Imperial College London (United Kingdom) and coordinated by the Imperial Clinical Trials Unit. The trial will be conducted in accordance with the principles of the Declaration of Helsinki and Good Clinical Practice and is approved by the independent National Research Ethics Committee London - Harrow (13/LO/0365). It is registered on the European Union Drug Regulating Authorities Clinical Trials database (EudraCT 2012-005159-18) and the International Standardised Randomised Controlled Trial Registry (ISRCTN12776039). The study is funded by the Efficacy and Mechanism Evaluation (EME) program of the National Institute for Health Research (United Kingdom)

The primary objectives of the trial are as follows: (1) to ascertain if levosimendan reduces the incidence and severity of organ dysfunction compared to placebo in adult patients who have septic shock; (2) to identify the effect of levosimendan on individual organ function in septic shock; and (3) to establish the safety profile and pharmacokinetics of levosimendan in this group of patients.

The secondary objectives of the study are: (1) to identify whether levosimendan reduces the need for and duration of catecholamine support and thus reduces myocardial injury; (2) to establish whether levosimendan alters the pro- and anti-inflammatory balance in sepsis; and (3) to collect long-term (3 and 6 month) survival data to help inform the appropriate long-term outcome measure for a subsequent effectiveness trial, should the efficacy of levosimendan be confirmed in this phase IIb trial.

### Inclusion criteria

The target population is adult patients (≥18 years) who require vasopressor support for the management of sepsis despite fluid resuscitation. Patients being treated on an ICU with suspected or confirmed infection will be eligible for the trial if they meet both of the following criteria:

Sepsis - fulfil two of the four criteria for the systemic inflammatory response syndrome (SIRS): (1) fever (>38°C) or hypothermia (<36°C); (2) tachycardia (heart rate >90 beats per minute); (3) tachypnea (respiratory rate >20 breaths per minute or PaCO_2_ < 4.3 kPa) or need for mechanical ventilation; (4) abnormal leukocyte count (>12,000 cells/mm^3^, <4000 cells/mm^3^, or >10% immature band forms).

Shock- hypotension, despite adequate fluid resuscitation, requiring treatment with a vasopressor infusion (such as norepinephrine, epinephrine, or vasopressin analogue) for at least 4 hours and still having an ongoing vasopressor requirement at the time of randomisation.

### Exclusion criteria

The presence of any of the following criteria will prevent entry into the study: more than 24 hours since meeting all of the inclusion criteria; end-stage renal failure at presentation (previously dialysis-dependent); severe chronic hepatic impairment (Child-Pugh class C); a history of Torsades de Pointes; known significant mechanical obstructions affecting ventricular filling or outflow or both; treatment limitation decision in place (such as Do Not Attempt Resuscitation or not for ventilation and/or dialysis); known or estimated weight >135 kg; known to be pregnant; previous treatment with levosimendan within 30 days; known hypersensitivity to levosimendan or any of the excipients; known to have received another investigational medicinal product within 30 days or currently in another interventional trial that might interact with the study drug.

### Primary outcome measure and sample size

This trial is designed to explore the efficacy and mechanism of action of levosimendan, as well as inform a subsequent effectiveness trial if appropriate. We will therefore examine organ dysfunction as measured by the Sequential Organ Failure Assessment (SOFA) score [2] as the primary endpoint (excluding the neurological component). We will compare mean SOFA scores between treatment groups. The mean SOFA in ICUs has been shown to be closely correlated to mortality and its predictive value was similar regardless of length of stay [3].

Our sample size of 500 patients will provide more than 90% power to detect a 0.5 point difference in the mean SOFA score assuming a SD of 1.5 [3]. In this previous validation study a 1 point rise in the mean SOFA score was associated with a significant mortality increase (mean SOFA 2.1 to 3.0 = 20%, 3.1 to 4.0 = 36.1% and 4.1 to 5.0 = 73.1% mortality; odds ratio 3.06, 95% CI 2.36 to 3.97). We will recruit an additional 3% (16 patients) to account for potential loss to follow-up and withdrawal of consent, as seen in previous UK ICU trials [37], giving a total of 516 patients with 258 in each arm (Figure 1).

**Figure 1 F1:**
[figure not shown]
**LeoPARDS proposed trial flow diagram.** CCMDS, Critical Care Minimum Data Set; ICU, Intensive Care Unit; SOFA, Serial Organ Failure Assessment.

### Secondary outcome measures

The SOFA score is a composite of several different organ failures and there may be differential effects of levosimendan in different organ systems. Therefore, in order to gain further insight into the mode of action of levosimendan we will also measure organ specific outcomes.

### Cardiovascular

We will compare oxygen delivery between treatment groups using central venous oxygen saturations (ScvO_2_). This will be measured and recorded at baseline, 6, and 12 hours, and then 12-hourly in all patients with an internal jugular or subclavian central venous catheter (CVC) for up to 96 hours, if the CVC remains *in situ*. The study will have more than 95% power to detect a 5% difference in ScvO_2_ assuming a SD of 15%.

Cardiac output monitoring using specified devices (PiCCO™, LiDCOplus™, esophageal Doppler, or pulmonary artery catheter) will be measured in select centers, at baseline, 6, 12, and 24 hours, and then 12-hourly for up to 96 hours or as long as the device is clinically required if shorter. Based on cardiac output data from the Vasopressin and Septic Shock Trial (VASST), a subgroup of 150 patients will provide more than 85% power to detect a 0.66 l.min^−1^.m^−2^ difference in cardiac index between treatment groups over this period assuming an SD of 1.3 [38]. We will also examine the effect of levosimendan in the subgroup of patients who have a low cardiac output at baseline, as evidenced by a low ScvO_2_ or measured cardiac output.

### Respiratory

Recent evidence has suggested levosimendan may also enhance calcium sensitivity in the diaphragm muscle and thus improve diaphragm contractility [39]. In those patients who require intubation and mechanical ventilation we will assess time to successful liberation from mechanical ventilation. This will be defined as: (1) extubated with face mask, nasal cannulae or room air, or (2) T-piece/heat and moisture exchange (HME) filter breathing, or (3) tracheostomy mask breathing, or (4) CPAP breathing ≤5 cm H_2_O without any pressure support or mandatory ventilation.

A total of 450 patients (90% of the sample size of 500) will provide 80% power to detect a hazard ratio of 1.4, based on the assumption that 63% of patients will be successfully liberated from mechanical ventilation by day 28.

### Renal

In view of the data demonstrating a beneficial effect of levosimendan on renal function in sepsis we will compare stages (0, 1, 2, and 3) of AKI using the Acute Kidney Injury Network (AKIN) definition [40]. Since death is clearly a worse outcome than renal failure, patients who have died will be categorized into a fifth stage. These five groups at day 14 will be analyzed as ordinal categorical data, using a constrained non-proportional odds model such that the log-odds ratios are assumed constant across all the cumulative probabilities except the last (death).

Power calculations have been undertaken using simulation with multi-state modeling based on previous data from previous septic shock trials [41-43]. These simulations suggested that the maximum difference in rates of AKI and death between treatment groups might be seen around day 14. The trial will have between 65 and 90% power to detect between 25 and 35% improvement in renal function with levosimendan.

### Secondary mechanistic outcomes

Serial blood and urine samples will be collected from patients at baseline, day 2, 4 and 6. Assays will include markers of AKI, myocardial dysfunction, inflammation, and intestinal perfusion. Possible assays are given below but as biomarker discovery is a very active area of research we will re-evaluate the best assays available at the time that study enrolment is complete and consider the use of additional or complementary biomarkers. Current possible assays include (1) AKI biomarkers in urine and plasma. Urinary Neutrophil Gelatinase-Associated Lipocalin (NGAL) is currently the best validated biomarker of AKI [44]. Alternative biomarkers of AKI (such as Kidney Injury Molecule-1 or cell cycle arrest biomarkers [45]) may be better characterised and validated by the end of the trial. (2) Markers of myocardial dysfunction. Serum B-type Natriuretic Peptide (BNP) has been demonstrated to be a reliable biomarker of myocardial injury, ischemia, and dysfunction in septic patients and also as a prognostic marker for a poor outcome [12,46]. (3) Biomarkers of systemic inflammation. This will be measured using a multiplex inflammatory biomarker assay. This will allow an assessment of the pro- and anti-inflammatory cytokine balance over time in patients with septic shock and allow a more detailed study of the other potential mechanisms of action of levosimendan. In addition, samples will be stored for subsequent analysis as appropriate.

### Pharmacokinetic substudy

The initial 80 patients enrolled in the study will have an additional 3 ml of blood collected while on ICU on days 2, 4, 6, 8, 10, 13 and 16 for assays of levosimendan and its active metabolite OR-1896. We will then compare the area under the curve (AUC) and the maximum concentration (C_max_) between patients with and without AKI and also with previous pharmacokinetic data from other studies. The drug and metabolite levels will be correlated to possible adverse hemodynamic events, namely tachycardia and hypotension. The independent Data Monitoring and Ethical Committee (DMEC) will be asked to suggest alternative dosing regimens if drug or metabolite levels are unexpectedly high in certain patient groups or if there is an association between infusion rates, drug levels, and adverse events. They will advise if any alternative dosing regimens should alter the sample size for the trial.

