### Administration of study drug

Patients will be randomized to receive an intravenous infusion of levosimendan at 0.05 to 0.20 μg.kg^−1^.min^−1^ or placebo for a period of 24 hours. The infusion will be prepared by diluting the contents of one vial of study drug in 500 ml of 5% dextrose. The study drug will not be started until the treating clinician is confident that adequate fluid resuscitation has been achieved and that the patient has reached their target blood pressure; this may be a mean arterial pressure (MAP) of 65 to 70 mmHg but may be increased or reduced if the treating clinician feels this is clinically necessary. The infusion will then be commenced at a rate of 0.1 μg.kg^−1^.min^−1^ based on actual (estimated) body weight. Although the summary of product characteristics states that an initial bolus of levosimendan should be given, in this trial the bolus dose will not be given to avoid hypotension and maintain patient safety. After 2 to 4 hours the infusion will be increased to 0.2 μg.kg^−1^.min^−1^ for the remaining 20 to 22 hours if there is no significant hypotension or tachycardia. Any initial hypotension will be treated with a fluid challenge and an increase in vasopressor dose if needed. Throughout the duration of the infusion, clinicians will have the option to reduce the infusion or stop it if they deem there to be significant hypotension or tachycardia. Details of the study drug infusion protocol are shown in Figure 2. Titration of the study drug dose between 0.05 and 0.2 μg.kg^−1^.min^−1^ will ensure patients receive an effective dose whilst minimizing adverse effects.

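### The pharmacokinetic sampling days cannot give a levosimendan AUC, and its Cmax depends on a day-2 draw that is not tied to the end of the infusion

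*Protocol article*

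**What the plan says.** The section Pharmacokinetic substudy takes an extra 3 ml of blood from the first 80 patients, "collected while on ICU on days 2, 4, 6, 8, 10, 13 and 16 for assays of levosimendan and its active metabolite OR-1896". It continues: "We will then compare the area under the curve (AUC) and the maximum concentration (C_max_) between patients with and without AKI". The two analytes are not separated at that point, so as written both measures apply to both. The results also have a safety use: "The drug and metabolite levels will be correlated to possible adverse hemodynamic events", namely tachycardia and hypotension, and the DMEC may be asked about other dosing regimens if levels turn out unexpectedly high. Pharmacokinetics is part of the third primary objective.

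Three other places bear on this:

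- The Background subsection Levosimendan says "The drug itself has a short plasma half-life of approximately 1 hour" and describes OR-1896 as a metabolite "which has an elimination half-life of approximately 80 hours".
- Administration of study drug gives levosimendan "or placebo for a period of 24 hours", with a rate step after 2 to 4 hours, and adds that "clinicians will have the option to reduce the infusion or stop it".
- The Abstract says "Eighty patients will have additional blood samples taken to measure levels of levosimendan and its active metabolites OR-1896 and OR-1855", whereas Pharmacokinetic substudy does not name OR-1855.

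**The concern.** The sampling days fit a substance that persists for days. OR-1896 does. Levosimendan, on the article's own half-life, is gone within hours of the infusion ending. The first listed sample falls on day 2, so the period that holds nearly all of the levosimendan exposure has no pharmacokinetic sample.

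If the levosimendan comparison reflects when the day-2 tube was drawn, it says little about whether AKI alters exposure. The safety correlation is exposed in a particular way. The infusion may be reduced or stopped for hypotension or tachycardia, and these are the events to be correlated with drug levels. A patient whose infusion was stopped for such an event before the draw would show a low level, which could weaken or reverse the association that the DMEC is asked to judge.

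For OR-1896 the question is different. Samples end when the patient leaves the ICU or dies, so an AUC taken to the last sample would depend partly on how long sampling lasted.

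**Working it through.** The article gives no precision or power figure for this substudy, so there is nothing to reproduce. The check uses first-order kinetics with the documented half-lives.

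**Inputs.** Levosimendan half-life 1 h and OR-1896 half-life 80 h (Levosimendan). Infusion of 24 h, rate 0.1 then 0.2 after s = 2 to 4 h (Administration of study drug). Sampling days from Pharmacokinetic substudy. Assumptions: one compartment, and day d means (d − 1) × 24 h after the infusion starts.

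**1. Which samples can contain levosimendan.** The fraction left h hours after the stop is 2^(−h). Day 4 is 72 h, which is 48 h after the stop: 2^(−48) ≈ 4 × 10^(−15). Even if the half-life were twice as long, 2^(−24) ≈ 6 × 10^(−8). Only day 2 remains.

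**2. Where the AUC lies.** Scale concentration so that the steady state equals the rate. Total AUC = 0.1s + 0.2(24 − s), which is 4.6 for s = 2 and 4.4 for s = 4. The part after the stop is 0.2/ln 2 = 0.289, or 6.3% and 6.6% of the total. So 93.7% and 93.4% accrues during the infusion.

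**3. What a trapezoid AUC would return.** Take zero at the start, C at the day-2 draw at time t, and effectively zero at 72 h. The area is ½·C·t + ½·C·(72 − t) = 36·C. It is the single day-2 concentration times a constant, so AUC and Cmax would be the same comparison in different units.

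| Day-2 draw (h from start) | Level, % of end-of-infusion | 36·C | % of true AUC (s = 2 to 4) |
|---|---|---|---|
| 24 | 100 | 7.2 | 157–164 |
| 26 | 25 | 1.8 | 39–41 |
| 30 | 1.6 | 0.1125 | about 2.5 |
| 36 | 0.02 | 0.0018 | 0.04 |

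**4. Cmax.** With an uninterrupted infusion the level at 24 h is above 99.9% of steady state, so a draw just before the stop captures Cmax. A draw 2 h after the stop reads 25% of it, and one 6 h after reads 1.6%. The same 1.6% applies to a patient whose infusion was stopped 6 h before the draw.

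**5. OR-1896.** With decline from 24 h, the share of the AUC captured by time T is 1 − 2^(−(T − 24)/80). Day 6 (T = 120): 1 − 2^(−1.2) = 0.565. Day 16 (T = 360): 1 − 2^(−4.2) = 0.946. The ratio is 0.565/0.946 = 0.60. The same calculation gives 36% of the day-16 value at day 4, 75% at day 8, 86% at day 10 and 95% at day 13. If the metabolite forms gradually, with an assumed formation half-life of 12 to 48 h (not in the article), day 4 captures 16–32% and day 6 captures 38–57% of the AUC to day 16. Sampling to day 16 then covers 89–94% of the total AUC.

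**The case against.** **Day 2 may already mean 24 hours.** The Abstract times the second mechanistic sample at 24 hours, and Secondary mechanistic outcomes calls the same sample day 2. The extra 3 ml is naturally read as added volume at that draw. Because the infusion waits for resuscitation and target pressure, a draw 24 h after inclusion would tend to fall late in the infusion. This stands as far as it goes. A reader might infer that the plan rules out a levosimendan Cmax, and it does not. But the substudy section never says that its draw is timed this way, nor ties it to infusion stop, and the infusion can be reduced or stopped early. Nor does the reading rescue the AUC, which is about 160% of the truth even at exactly 24 h.

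**A model could supply the AUC.** Delivered dose divided by clearance would give one. It would rest on the same single concentration plus the dosing record, so it still needs the draw before the stop and a logged infusion history.

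**The OR-1896 method is simply not stated.** True. The truncation matters only if the AUC is taken to the last ICU sample, and the full protocol or analysis plan may specify something else. A reader might also infer that AKI patients will show inflated OR-1896 exposure because they stay longer. The article gives no figure linking AKI to ICU stay, and its Background says AKI doubles the risk of death, which shortens sampling. The direction is unknown.

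**The number on active drug.** With 1:1 allocation about 40 of the 80 patients will have drug levels. A reader might call this a shortfall, but the article never says that 80 receive levosimendan and claims no power for the substudy. It is not an error.

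**Conclusion.** The point holds for the levosimendan AUC. On the article's own half-life and infusion length, one sample at most contains the drug and 93–94% of the exposure is unsampled, so this stated measure cannot be delivered from the stated schedule. That is a mismatch inside the plan, not detail left to another document. It rests on simple first-order kinetics and is not sensitive to the exact half-life.

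For Cmax the conclusion is conditional: it is recoverable from a draw just before an uninterrupted infusion ends, and otherwise is understated, by a factor of four at 2 h after the stop.

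For OR-1896 the schedule is suitable if complete. The need there is for an AUC method that does not depend on length of sampling, with no presumption about which AKI group would be favoured. The OR-1855 discrepancy is a minor separate inconsistency. None of this touches the primary SOFA outcome, but it does bear on a primary objective and on information that the DMEC may act on.

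**What to change.** - Tie the existing day-2 pharmacokinetic draw to the end of the infusion, before it stops.
- Record clock times of the draw, every rate change and the stop. Where the infusion ended before the draw, report the level with time since stop and do not treat it as Cmax.
- Drop the levosimendan AUC and report the end-of-infusion concentration. Give clearance as rate divided by concentration only where the rate had been stable for several half-lives.
- Keep AUC for OR-1896, but compute it over a common window, by extrapolation or with a population-PK model, not to the last ICU sample.
- Make the Abstract and Pharmacokinetic substudy agree on whether OR-1855 is assayed.

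The cost is a change to the sampling instructions and the pharmacokinetic analysis wording, with no extra samples. Sites must time one existing draw and log infusion changes, and no levosimendan AUC is reported.

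### Infusion rates and drug levels are partly set by the hypotension and tachycardia they will be correlated with, which biases the DMEC's association trigger toward a protective sign

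*Protocol article*

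**What the plan says.** Three statements in the protocol article bear on this.

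- **Analysis (Pharmacokinetic substudy).** "The drug and metabolite levels will be correlated to possible adverse hemodynamic events, namely tachycardia and hypotension". Samples come from the first 80 patients and are "collected while on ICU on days 2, 4, 6, 8, 10, 13 and 16 for assays of levosimendan and its active metabolite OR-1896".
- **Decision (same section).** The DMEC is asked to suggest alternative regimens on either of two grounds. One is that "drug or metabolite levels are unexpectedly high in certain patient groups". The other applies "if there is an association between infusion rates, drug levels, and adverse events". It also advises whether a new regimen should change the sample size.
- **Titration (Administration of study drug).** The infusion starts at 0.1 μg/kg/min. After 2 to 4 hours it rises to 0.2 "for the remaining 20 to 22 hours if there is no significant hypotension or tachycardia". Throughout, "clinicians will have the option to reduce the infusion or stop it if they deem there to be significant hypotension or tachycardia". The same section says: "Any initial hypotension will be treated with a fluid challenge and an increase in vasopressor dose if needed".

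The article does not say that exposure will be taken before the event, or that titration will be allowed for.

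**The concern.** The two events named as outcomes in the exposure analysis are the two events that determine exposure. A patient who becomes hypotensive or tachycardic may miss the step-up, have the rate reduced, or have the infusion stopped, and so tends to have a lower mean rate, total dose and later level. The event then partly explains the low exposure, the opposite of the direction that the correlation is meant to test.

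Sampling does not remove the problem. The first sample is on day 2, so levels are measured after the titration decisions. The parent drug's half-life of about 1 hour means that the sample says little about the level when an early event began. The metabolite, with a half-life of about 80 hours, largely follows total dose, which titration also sets.

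At stake is how the DMEC reads the association ground. A null or protective-looking result from the first 80 patients could be taken as reassurance about dosing for the other 436 (516 - 80).

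**Working it through.** **Inputs from the article.** Rates of 0.05 to 0.2 μg/kg/min over 24 hours; step-up at 2 to 4 hours; parent half-life about 1 hour; 80 substudy patients randomized 1:1, so about 40 on active drug. The article gives no figure for the strength of this correlation, so there is none to reproduce.

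**Dose over 24 hours** (rate × 60 × hours):
- No event: 0.1×60×4 + 0.2×60×20 = 264, up to 0.1×60×2 + 0.2×60×22 = 276 μg/kg.
- Held at 0.1: 0.1×60×24 = 144.
- Cut to 0.05 at 2 hours: 12 + 0.05×60×22 = 78.
- Stopped at 2 hours: 0.1×60×2 = 12.

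A patient whose rate is changed for an event can thus receive from about half (144/276 = 52%) to under 5% (12/264 = 4.5%) of the full dose, whether or not the drug caused the event.

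**Parent drug left 5 hours after a stop:** 0.5^5 = 3%.

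**Simulation of 40 active patients, 1000 runs per scenario.** The following are assumptions, not document figures: event hazard 0.01 per hour at zero concentration; true hazard ratio (HR) 1, 2 or 4 at the typical steady-state level for 0.2; log-SD of clearance 0.3 or 0.6; patient frailty log-SD 0.5; step-up at 3 hours unless the rate was already cut; a cut either halves the rate (not below 0.05) or stops it; metabolite proportional to total dose and not itself a cause of events. The share of events leading to a cut was 0, 25, 50 or 100%. Mean correlations with having an event were:

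| True HR | Events leading to a cut | 24-hour level | Mean infusion rate | Metabolite |
|---|---|---|---|---|
| 2-4 | none | +0.11 to +0.39 | no variation | -0.01 to 0.00 |
| 2-4 | 25-50% | -0.44 to +0.28 | -0.29 to -0.54 | -0.05 to -0.35 |
| 2-4 | all | -0.12 to -0.90 | -0.75 to -0.83 | -0.24 to -0.67 |
| 1 | 25-100% | -0.08 to -0.81 | -0.41 to -0.86 | -0.06 to -0.59 |

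The rows for a harmful and a harmless drug overlap widely, so neither the sign nor the size of the correlation separates them.

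**Check of the remedy.** In the same simulations, first events were divided by event-free time at rates above 0.1 and at rates of 0.1 or less. The ratio of the two event rates was 0.92-1.02 for HR 1, 1.42-1.81 for HR 2 and 2.24-2.54 for HR 4. These lie below the HR because 0.2 is compared with 0.1, not with zero (for a typical patient √2 = 1.41 and √4 = 2). The direction was right in every scenario.

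One caution applies. Before the first event the rate is almost a function of time, 0.1 early and 0.2 later, and the simulation held the background hazard constant. If that hazard were twice as high in the early hours (an assumption), the ratio would roughly halve, so 1.42-1.81 would become about 0.7-0.9. The same trend would appear under placebo infusion, so the placebo patients are needed as a control.

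**The case against.** The case against has several parts.

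- **Rate cuts are not automatic.** Initial hypotension is met with fluid and vasopressor, and reducing or stopping is an option for events judged significant. This stands. A reader might infer that patients with events must have lower levels by protocol, so that the correlation is bound to be reversed. The article does not support that: with 25-50% of events leading to a cut, the level correlation could still be positive.
- **Harm would not simply be masked.** This also stands. The high-levels ground does not use events, although early cuts can lower the levels seen. The association ground states no direction, so a strong negative association would formally meet it, though it would be easy to misread. Under Statistical analysis and trial oversight, the DMEC also reviews adverse events, outcomes and compliance every six months, in a randomized, placebo-controlled trial.
- **Later metabolite data are less exposed.** Six of the seven sampling days fall on day 4 or later, and events after the infusion cannot feed back on dose. This stands in part, because total dose still carries the earlier titration.
- **Sample timing is loose.** No clock time is given for day 2. The Abstract puts the matching mechanistic sample at 24 hours, so day 2 may be the end of the infusion. The argument does not need it to be later.
- **Time order may be left to the full protocol or analysis plan.** This does not dispose of the point. The article itself fixes the exposure, outcomes, sampling days and the decision attached, and that combination is exposed to reverse causation.

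**Conclusion.** The point holds in a limited form. Because titration responds to the events under study, a plain correlation of rates or day-2-onward levels with hypotension and tachycardia is biased toward a protective sign, and it may be weakened, null or reversed when the drug does cause events. Whole-infusion mean rate was negatively correlated in every scenario with cuts. The level correlation depended on the share of events leading to a cut and on the spread of clearance, neither of which the article gives. The sizes are therefore illustrative and rest on the stated assumptions; the direction of the bias follows from the titration text alone.

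The consequence is confined to the association ground of the DMEC trigger. This is an analysis change worth making, not evidence that the trial would miss harm.

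**What to change.** Amend the Pharmacokinetic substudy text, or the plan that implements it, as follows:

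1. Relate each patient's first event during the infusion to the infusion rate, or model-predicted level, just before onset.
2. Relate metabolite levels only to events after the sample.
3. Give the DMEC, alongside, the levosimendan-versus-placebo comparison of first-event rates, and of the rate-event association with placebo infusions as negative control.
4. Label correlations with levels measured after an event as descriptive.

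The cost is mainly analysis wording. It needs timed records of rate changes and event onsets, which are assumed to exist; the article does not say so. A model-predicted level needs more modelling than the rate, since sampling starts only on day 2. Precision will be low with about 40 active patients, so the result should be given with its interval and read beside the randomized comparison. No change to dosing or titration is proposed.
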